### Outcome parameters

Our primary endpoint is the percentage of patients with normalization of Hb-level from start treatment until surgery (Hb >12 g/dl (7.5 mmol/L) for women and Hb >13 g/dl (8.0 mmol/L) for men). Our secondary endpoints are morbidity, assessed with the Comprehensive Complication index, amount of blood transfusions needed, length of stay, absolute change in HB from baseline prior to surgery and postoperatively, time needed to achieve normalization of Hb-level, change in baseline of other iron/haematological parameters (TSAT, ferritin, CRP), health-related quality of life and fatigue scores (EQ-5D, EORTC-C30, EORTC -CR29 iMCQ, BFI & iPCQ), relation between anaemia and Glasgow Prognostic Score (derived from CRP and Albumin) and cost-effectiveness of intravenous iron treatment compared to oral. Blood samples to assess Hb- and iron values will be taken at baseline, at admission, postoperative day 1, 7 and after 1-,2- and 3 months.

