### Sample size calculation

The principal analysis will be an intention-to-treat comparison of the proportions of patients with iron deficiency anaemia between the two study groups. The trial is designed as a superiority trial, hypothesizing a greater percentage of patients achieving normalization of Hb-level (called ‘responder’) in favour of infusion of ferric(III)carboxymaltose compared to oral iron suppletion. Our power calculation is based on the study of Seid et al. [24], which compared ferric(III)carboxymaltose with oral ferrous sulphate in a population of post-partum women with an iron deficiency anaemia. The proportion achieving a normalization of Hb after two weeks of treatment was 55 % in the intravenous iron group and 35 % in the oral iron group. We expect that the efficacy of the iron therapy is lower in patients with a colorectal carcinoma. Therefore, the expected percentage of patients who achieve normalization of Hb-level (Hb >7.5 mmol/l (12 g/dl) for women and Hb >8.0 mmol/l (13 g/dl) for men) is 45 % in the intravenous iron group and 25 % in the oral iron group. Based on these proportions, a sample size of 89 patients per group is needed for a Chi square test to achieve 80 % power at a two sided alpha of 0.05. With an estimated loss to follow up of 10 %, a sample size of 198 is calculated. We used nQuery advisor version 7.0 to calculate the sample size.

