### Data-analysis

The intention-to-treat population will include all patients who give their informed consent, for whom there is confirmation of successful allocation of a randomization number, and who received at least one dose of the study medication. Statistical analyses will be performed using SPSS software for Windows version 19.

The primary endpoint, the percentage of patients with a normalised Hb-level at admission will be compared between the two study groups on a intention to treat basis. Using a two-sided Chi-square test at a significance level of 0.05. All data will be collected in an electronic database. The outcome parameters will be analysed with appropriate statistical tests by a statistician blinded for the treatment allocation using the statistical program SPSS software for Windows version 19.

Appropriate summary descriptive statistics will be determined for all secondary endpoints at each visit using raw scores. To assess morbidity the continuous scale of the Comprehensive Complication Index [25] and the categorical Clavien-Dindo classification will be used, for which appropriate statistical tests will be undertaken (the Mann Whitney U test, in case of non-normal distribution, and the Chi squared test respectively). For continuous secondary endpoints, either analysis of variance or analysis of covariance models will be used and where necessary, the repeated measures procedure will be implemented.

Quality of life data (e.g. EORTC-C30, EORTC-CR29 and EQ-5D) will be graphically represented across all time points and analysed using a repeated measures analysis of variance. All tests based on proportions will be analysed using a logistic regression model with treatment as a factor and, where appropriate, other specified covariates to include baseline score. Time-to-event will be analysed with use of Kaplan-Meier Survival analysis and compared using the log-rank test. Where appropriate, a stratified log-rank test and Cox proportional hazard model will be used to explore the potential influences of baseline HB and other specified covariates.

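### The chi-square on Clavien-Dindo and the repeated-measures ANOVA on quality of life use less of the collected data than alternatives in the same software (cheap improvement, secondary analyses only)

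*Protocol article*

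**What the plan says.** All statements are in the protocol article.

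- **Morbidity endpoint (Outcome parameters):** "Our secondary endpoints are morbidity, assessed with the Comprehensive Complication index". Clavien-Dindo is not in that list.
- **Morbidity tests (Data-analysis):** alongside the Index, "the categorical Clavien-Dindo classification will be used". The tests follow in the same order: Mann-Whitney U for the Index "in case of non-normal distribution, and the Chi squared test respectively" for Clavien-Dindo. No grouping, cut-off or ordinal test is named.
- **Quality of life (Data-analysis):** the questionnaire data will be "graphically represented across all time points and analysed using a repeated measures analysis of variance". The text gives no rule for missed assessments. The visit schedule is in Figure 2, which is not available here.
- **Other continuous outcomes (Data-analysis):** "For continuous secondary endpoints, either analysis of variance or analysis of covariance models will be used", with a repeated-measures procedure where needed. No rule for choosing between the two models is given.
- **Software (Data-analysis):** "Statistical analyses will be performed using SPSS software for Windows version 19".

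**The concern.** Three choices give up information that the trial will have collected.

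1. Clavien-Dindo grades run from no complication to death. A Pearson chi-square treats them as unordered labels, so a consistent shift towards milder grades is spread over several degrees of freedom and many sparse cells.
2. The classical repeated-measures ANOVA, including the SPSS general linear model version, needs a full set of assessments per patient. Follow-up runs to six months after cancer surgery, so some missed questionnaires are foreseeable.
3. For outcomes with a baseline value, ANOVA without baseline stays open beside ANCOVA, which is normally more precise.

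The primary endpoint is a laboratory threshold. Morbidity, quality of life and fatigue are where the Methods/design section hopes to see clinical benefit, so the efficiency of their analysis matters.

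**Working it through.** **1. The plan's own figure.** Inputs from Sample size calculation: 45% versus 25%, "80 % power at a two sided alpha of 0.05", 10% loss.

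n = [1.96·√(2·0.35·0.65) + 0.8416·√(0.45·0.55 + 0.25·0.75)]² / 0.20² = (1.322 + 0.555)² / 0.04 ≈ 88.1, so 89 per group. 89 / 0.90 = 98.9, so 99 per group and 198 in total. This reproduces the plan. No power figure is given for the secondary tests.

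**2. Clavien-Dindo.** The protocol gives no grade distribution, so the following is assumed: control arm 60/12/13/4/5/2/2/2% over eight categories, 89 per arm, common (proportional) odds ratio, 3,000 simulated trials per odds ratio, two-sided 0.05.

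| Test | OR 1.5 | OR 1.8 | OR 2.0 |
|---|---|---|---|
| Chi-square, eight categories | 9% | 19% | 26% |
| Chi-square, none / I–II / III or above | 19% | 36% | 48% |
| Chi-square, any versus none | 25% | 44% | 56% |
| Chi-square, III or above versus lower | 14% | 24% | 32% |
| Mann-Whitney | 25% | 46% | 59% |

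A repeat at odds ratio 2.0 gave 25, 47, 57, 31 and 59%, so differences of a point or two are simulation error.

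Hand check of any versus none at odds ratio 2.0: the odds of no complication go from 0.60/0.40 = 1.5 to 3.0, so complications fall from 40% to 25%. The pooled rate is 0.325. Power = Φ{[0.15 − 1.96·√(2·0.325·0.675/89)] / √[(0.24 + 0.1875)/89]} = Φ{(0.15 − 0.1376)/0.0693} ≈ 57%, which agrees.

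Sparseness: a 5% category has an expected count of 89 × 0.05 = 4.45 in the control arm and a 2% category 1.78. Five of the eight control cells are therefore below 5. Over both arms the simulated share was about 58%.

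A second set of assumptions (99 per arm, seven grades, any-complication rate 30/40/50%, 4,000 trials each) gave 26/33/39% for the ungrouped chi-square and 55/62/70% for Mann-Whitney at odds ratio 2.0. A cut at grade III or above gave 28/31/37%. With no true difference, Mann-Whitney rejected in 5.1–5.3% of trials and the ungrouped chi-square in 3.7–4.5%, so the rank test's gain does not come from excess false positives.

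**3. Quality of life.** The number remaining in a complete-case analysis depends on inputs the text does not give.

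- If the stated 10% loss were all the missing data: 198 × 0.90 ≈ 178 patients.
- If each of V assessments is missed independently with probability m, the complete share is (1 − m)^V. With V = 4 and m = 5%, 0.95⁴ = 0.815 (161 patients). With V = 6 and m = 15%, 0.85⁶ = 0.377 (75 patients). Both V and m are assumed.

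To turn this into power, take a constant treatment effect and equal correlation ρ between visits. The efficiency of complete cases relative to all available data is

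[(1 − m)^V · V/(1 + (V − 1)ρ)] / Σₖ C(V,k)(1 − m)^k m^(V−k) · k/(1 + (k − 1)ρ).

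For V = 5, m = 10%, ρ = 0.5 this is 0.604. A comparison with 80% power on all data then has Φ(2.802·√0.604 − 1.96) ≈ 59%. Over V = 4–5, m = 5–15% and ρ = 0.5–0.7 the range is about 47–72%. If only the stated 10% is lost, efficiency is at least 0.90 and power at least Φ(2.802·√0.90 − 1.96) ≈ 76%.

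**4. ANOVA or ANCOVA.** With equal variances and baseline-to-outcome correlation ρ, the treatment-effect variance relative to an unadjusted follow-up comparison is 2(1 − ρ) for a change score and 1 − ρ² for ANCOVA. At an assumed ρ of 0.5 these are 1.00 and 0.75; at 0.7 they are 0.60 and 0.51.

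**The case against.** The strongest reply on morbidity is that the listed endpoint is the Comprehensive Complication Index, a graded score already planned with a rank test if non-normal. That stands. A reader might infer that the trial as planned can hardly detect morbidity differences; the documents do not support this, because the point reaches only the added Clavien-Dindo analysis. It also stands that the size of the loss depends on grouping. Any versus none costs almost nothing under the assumed grades, and an unseen analysis plan may set a grouping. It does not follow that every grouping is harmless: a cut at grade III or above loses about as much as no grouping.

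On quality of life, the protocol names neither listwise deletion nor a specific SPSS procedure, and rules for missed visits are commonly left to the analysis plan. That stands. A reader might infer that the sickest patients will be dropped, or that only some 59–77% will be analysed (0.90⁵ and 0.95⁵). Neither is in the document: the first is plausible but not shown, and the second assumes five visits and independent missingness. Sphericity adds little, since corrections exist and the overall between-arm test does not depend on it. What remains is that "analysed using a repeated measures analysis of variance" names a method whose standard form needs complete data.

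On baseline adjustment, the wording permits ANCOVA, ANOVA is valid under randomisation, and an ANOVA on Hb change already uses baseline by subtraction. This part is therefore a matter of efficiency, not an error.

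Finally, the protocol says secondary findings will be read as patterns without undue weight on single results, which limits the consequence.

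**Conclusion.** The point holds as a cheap improvement of minor severity. The named chi-square discards the order of the Clavien-Dindo grades. Under the assumed distribution at odds ratio 2.0 this means about 25% power ungrouped against about 59% for a rank test, with the loss running from negligible to about half according to a grouping the text does not state. The named repeated-measures ANOVA in its standard form analyses complete cases. That means about 178 of 198 patients if the stated 10% is all that is missing, and fewer by an amount that cannot be fixed from the text if single visits are also missed. Leaving ANOVA without baseline open gives up some precision.

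The direction for Clavien-Dindo held in every scenario tried without grouping. The sizes rest on assumed grade distributions, proportional odds, visit numbers, missingness and correlations. Only secondary analyses are touched; the primary chi-square test, the 89 per group and the total of 198 stand.

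**What to change.** Change the wording of Data-analysis, or settle it in the analysis plan before outcome data are seen:

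- **Clavien-Dindo:** compare arms with a Mann-Whitney test or a proportional-odds model on the ordered grades, and tabulate the grades descriptively. If a grouped chi-square is kept, state the grouping in advance.
- **Quality of life, fatigue and serial Hb:** use a likelihood-based mixed model for repeated measures with treatment by visit, baseline value by visit, the stratification factors and an unstructured covariance. SPSS MIXED fits this and keeps patients with some missed visits.
- **Single-time-point continuous endpoints with a baseline value:** use ANCOVA with that value as covariate, and remove the open choice.

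The cost is a little more analysis work and a missing-at-random assumption for the mixed model, which is weaker than what a complete-case analysis requires. No extra patients, visits or software are needed.

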### The primary aim of the FIT trial

To compare the percentage of patients with normalization of Hb-level (>12 g/dl (7.5 mmol/l) for women and > 13 g/dl (8 mmol/l) for men) after intravenous versus oral iron therapy in patients undergoing curative surgery for colorectal carcinoma.

Secondary aims of the FIT trial are:2)To analyse the effect of preoperative iron therapy (intravenous versus oral) on postoperative morbidity, length of stay, amount of blood transfusions needed and quality of life and fatigue scores.3)To determine the cost effectiveness of preoperative intravenous iron substitution in comparison with oral substitution.

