### Study design

The study is designed as a multicentre randomized clinical trial comparing ferric(III)carboxymaltose infusion with oral supplementation of ferrofumarate in the treatment of preoperative anaemia in colorectal cancer patients. Patients with a proven iron deficiency anaemia who undergo segmental colonic resection or (low) anterior resection because of M0-stage colorectal carcinoma are eligible for inclusion. Patients undergoing local excision of a rectal carcinoma (TEM/EMR/ESR) will not be included. In Fig. 1 you can find the flowchart of the FIT-trial.

When a patient has got a proven iron deficiency anaemia and the patient does not meet the criteria for exclusion, he/she will be included in the trial. Written informed consent will be obtained from each patient. The patients’ albumin and C-reactive protein (CRP) levels are used to derive a Glasgow Prognostic Score (GPS) which can be used as a predictor of post-operative outcome.

Patients will be computer randomized in random blocks of sizes 2 or 4 for either intravenous- or oral iron. Randomization will be stratified for age, colon or rectal carcinoma, open or laparoscopic operation and baseline Hb (8–10 g/dl vs 10–13 g/dl).

Apart from routine 5 year oncological follow-up, patients will be followed more intensively until 6 months after surgery as part of this trial. Hb, transferrin saturation (TSAT), ferritin, Hematocrit and CRP levels are measured at postoperative day 1, day 7, at 4, 8 and 12 weeks to monitor the anaemia.The follow-up schedule is detailed in Fig. 2.

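### Quality-of-life scores are assigned a repeated-measures analysis of variance with no baseline covariate; adjusting for the baseline score would gain precision at almost no cost

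*Protocol article*

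**What the plan says.** Quality of life and fatigue belong to a stated secondary aim (section on the primary aim of the trial: "amount of blood transfusions needed and quality of life and fatigue scores") and are listed again under Outcome parameters as "health-related quality of life and fatigue scores".

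The Data-analysis section has three consecutive statements that bear on how these scores are compared:

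- General rule: "For continuous secondary endpoints, either analysis of variance or analysis of covariance models will be used", with a repeated-measures procedure where necessary. No covariate is named, and no rule is given for choosing between the two.
- Quality of life: the data "will be graphically represented across all time points and analysed using a repeated measures analysis of variance". No covariate is named. The text does not say whether baseline is one of the repeated levels, or whether the treatment main effect or the treatment-by-time interaction is the test.
- Proportions: logistic regression with treatment and, "where appropriate, other specified covariates to include baseline score".

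The measurement times for the questionnaires are not in the readable text; Study design says "The follow-up schedule is detailed in Fig. 2", and that figure is not shown here.

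**The concern.** In a randomised comparison of a score measured before and after treatment, the baseline value usually predicts the later values. Adjusting for it removes variance that has nothing to do with treatment. The quality-of-life sentence uses the one of the two named model families that carries no covariate, while the baseline score is named only for proportions.

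A repeated-measures analysis of variance without a covariate can be run in three ways:

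- (a) Baseline is a time level and the treatment main effect is tested. The effect is averaged with a pre-treatment visit at which randomisation makes the expected difference zero, so the estimate is diluted.
- (b) Baseline is a time level and the treatment-by-time interaction is tested. Baseline then enters as part of a contrast, and the test spends one degree of freedom per post-baseline visit.
- (c) Baseline is left out and its prognostic information goes unused.

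At stake is the chance of detecting, and under (a) the estimated size of, a quality-of-life benefit that the trial names among its hypotheses.

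**Working it through.** **The plan's own figure.** The only power statement concerns the primary endpoint: 45% v 25%, "to achieve 80 % power at a two sided alpha of 0.05". With pooled variance and no continuity correction, n = [1.96·√(2·0.35·0.65) + 0.8416·√(0.45·0.55 + 0.25·0.75)]² / 0.20² = (1.322 + 0.555)² / 0.04 = 88.1, so 89 per group. Then 89/0.9 = 98.9, so 99 per group and 198 in total. This reproduces. No power is stated for quality of life.

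**Assumptions for quality of life (none given in the document).** A baseline score is collected; 89 per arm with complete data; unit variance and the same correlation ρ between all visits; k visits including baseline, of which m = k − 1 are after baseline; a constant effect d (in SD) at every post-baseline visit.

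**Variances per patient**

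- Post-baseline mean: (1 + (m−1)ρ)/m
- Post-baseline mean adjusted for baseline: the same minus ρ²
- Mean over all k visits: (1 + (k−1)ρ)/k, with the effect reduced to d·m/k

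**Example: ρ = 0.5, k = 5, m = 4.** The three variances are 0.625, 0.375 and 0.600. The effect is set so that the adjusted comparison has 80% power: d = 0.257, since √(2·0.375/89) = 0.0918 and 0.257/0.0918 = 2.80.

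| Analysis | Calculation | Power |
|---|---|---|
| Adjusted mean difference | 0.257/0.0918 = 2.80 | 80% |
| (a) Main effect, baseline included | effect 0.257·4/5 = 0.206; SE √(2·0.600/89) = 0.116; ratio 1.77 | about 42% |
| (b) Interaction | noncentrality (89/2)·(0.257²·4/5)/(1−0.5) = 4.70; F with 4 and 704 df | about 37% |
| (c) Post-baseline only | SE √(2·0.625/89) = 0.1185; ratio 2.17 | about 58% |

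Under (a) the estimate is also 4/5 of its true size. Adjustment brings the variance of the post-baseline mean to 0.375/0.625 = 0.60 of its unadjusted value.

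**Range, with the constant effect kept.** Over ρ 0.3 to 0.7 and 3 to 6 visits, again with the adjusted comparison at 80%: (a) 24–57%, (b) 24–60%, (c) 39–74%.

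**Effect shape.** The same setting (ρ = 0.5, five visits, 89 per arm) with other assumed effects at the four post-baseline visits. The joint test is the baseline-adjusted test of any difference over the four visits.

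| Effects (SD) | Unadjusted interaction | Adjusted average over visits | Adjusted joint test |
|---|---|---|---|
| constant 0.257 | 37% | 80% | 60% |
| 0.5, 0.25, 0, 0 | 94% | 53% | 96% |
| 0.6, 0.3, 0.1, 0 | 98% | about 77% | 99% |
| 0.4, 0.3, 0.2, 0.1 | about 66% | about 77% | 80% |

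The unadjusted interaction beats the adjusted average when the effect is early and fades. That reversal comes from which term is tested, not from the adjustment: the adjusted joint test beats the unadjusted interaction for every shape tried.

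**Single change from baseline (relevant to Hb, TSAT, ferritin).** The variance of a change score is 2(1−ρ); with analysis of covariance it is 1−ρ². If analysis of variance on change has 80% power, analysis of covariance has 93.5%, 89.9%, 86.0% and 84.0% at ρ = 0.3, 0.5, 0.7 and 0.8.

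**The case against.** The strongest reply is that the document does not exclude baseline adjustment. Its general rule for continuous secondary endpoints already admits analysis of covariance with repeated measures, and quality-of-life scores are such endpoints. The phrase about all time points describes the graph, so it does not show that baseline is an outcome level. A condensed article may leave the role of baseline and the tested term to the analysis plan. Unadjusted analysis of variance is also valid in a randomised trial, and quality of life is one of many unpowered secondary endpoints, which the article says it will read as patterns alongside the primary result.

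Much of this stands. A reader might infer that the plan forbids adjustment; it does not. A reader might also infer that baseline must be either averaged into the outcome or discarded. The interaction test is neither, because baseline enters it as a contrast. Nor can a minimum loss be claimed under every reading: the comparison with the adjusted average assumes a constant effect, which the document does not support or give. Study design has patients followed to six months after surgery, and Study procedures provides further iron in the allocated arm for those still anaemic, so other shapes are plausible.

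What the reply does not remove is that the article gives quality of life its own method, and that method carries no covariate, between two sentences showing that adjustment was in view. The point concerns the method stated, not detail left out.

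**Conclusion.** The point holds as a cheap improvement to the stated method. Provided a baseline score exists, each unadjusted version is less precise than its baseline-adjusted counterpart, and the main effect that includes the baseline visit is also biased toward zero.

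The figures of about 42%, 37% and 58% against 80% illustrate one set of assumptions (89 per arm, complete data, ρ 0.5, five visits, constant effect). They do not estimate this trial's loss, because the correlation, the number of visits and the effect shape are all unknown here. The consequence is limited to secondary endpoints for which no power was planned. Nothing here supports a doubt about the validity of the primary chi-square comparison or the total of 198.

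**What to change.** Replace the quality-of-life sentence in Data-analysis with wording to this effect: post-baseline quality-of-life and fatigue (BFI) scores will be analysed in a repeated-measures model with treatment, visit, treatment-by-visit and the baseline score of the same scale as covariate; baseline is not an outcome visit. Baseline-adjusted treatment differences will be reported at each visit and as an average over visits.

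State in advance which of these is the main test, since an average over visits can miss an early effect that wanes.

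For change from baseline in Hb, TSAT and ferritin, use the analysis of covariance option already listed, with the baseline value as covariate.

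The cost is a few sentences of analysis text, with no new data or patients. The small downside is that a patient without a baseline score needs a simple baseline imputation to stay in the model.
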